### Intervention

Participants receive either azithromycin (Zithromax) or placebo, both donated by the Pfizer Corporation. Both have the same appearance and colour, but the placebo contains no active substance. Study medication is reconstituted at the time of dosing and administered under direct observation in oral suspension form.

Pregnant participants are dosed with 50 mL of reconstituted liquid, equivalent to 2 g of study medication. Infants are dosed 20 mg/kg up to a maximum of 1 g, consistent with the recommended dosage for MDA.^10^ Infant doses are calculated by the electronic data collection form according to the infant’s weight at the study visit. Participants are observed for 30 min after receiving each dose. Participants who have an allergic reaction to the study medication are given medical attention as appropriate and are retained in the study but do not receive additional doses.

Dosing time points are aligned with routine healthcare visits. A minimum 72-hour window is required between doses. Pregnant participants receive up to three single doses over the course of the study, composed of 1–2 antenatal doses and a dose at delivery (table 2).

**Table 2 T2:** Study schedule

Time point	ANC visit ≥14 weeks gestation	Second ANC visit	Delivery	1 week after delivery	Penta-1 visit (approx. 6 weeks after delivery)	Penta-3 visit (approx. 14 weeks after delivery)	6 months after delivery	12 months after delivery*
Mother–infant cohort participants								
Eligibility assessment and informed consent	M							
Randomisation	M/I							
Administration of study medication	M	M	M		I	I		
Demographic Questionnaire	M							
Medical history	M	M	M		M/I	I		
Labour and Delivery Questionnaire			M/I					
Weight measurement			I		I	I		
Vital status assessment		M	M/I	I	M/I	I	I	I

Infant-only cohort participants								
Eligibility assessment, informed consent and randomisation					I			
Administration of study medication					I	I		
Demographic Questionnaire					I			
Medical history					I	I		
Weight measurement					I	I		
Vital status					I	I	I	I

*Infants who reach 12 months of age before the end of follow-up have a final vital status assessment at 12 months. All other infants have a final vital status assessment at the end of the study follow-up period when they are between 6 and 12 months of age.

ANC, antenatal care; I, infant participant; M, mother participant; Penta-1, first pentavalent vaccination; Penta-3, third pentavalent vaccination.

Ideally, pregnant participants are dosed in the second and third trimesters, but to accommodate individual variations in ANC timing, the first dose is administered at the enrolment ANC visit and the second dose at the next routine ANC visit or at delivery, whichever occurs sooner. The delivery dose is given during labour when possible but may be administered within 24 hours after delivery regardless of whether the infant is stillborn or liveborn. Infants are dosed when they present to a study facility to receive their first and third doses of pentavalent vaccine. Infants must be at least 6 weeks of age to receive the first dose of study medication.

### Follow-up and primary outcome measurements

The primary study outcomes are a composite of stillbirths and infant deaths for aim 1A, and infant deaths for aim 1B. Stillbirths are defined according to the WHO early stillbirth definition, that is, the birth of a fetus with no signs of life at ≥22 weeks gestation, or the birth of a fetus with no signs of life weighing at least 500 g.^18^ Birth outcomes are recorded for every enrolled participant at the delivery visit. Participants who miss the delivery visit are followed up at least three times to ascertain the birth outcome.

Infant deaths are defined as any death of a liveborn infant in the first year of life, with infant vital status assessed at multiple time points (table 2). All enrolled infants are followed through at least 6 months of age. Study follow-up ends when the last enrolled infant reaches 6 months of age. At that point, all infants between 6 and 12 months of age will have a final vital status assessment. Infants who reach 12 months of age before the end of the trial will have a final vital status assessment at 12 months. Participants with a 6-month vital status that is unknown after at least three contact attempts by the study team are considered lost to follow-up.

### Secondary outcome measurements

Secondary outcomes include low birth weight (<2500 g), gestational age at birth (online supplemental appendix table 3), neonatal death (0 to <28 days) and a composite outcome of maternal hospitalisations and mortality through 6 weeks post partum. The cost-effectiveness of the interventions will also be estimated as a secondary aim.

### Safety monitoring and adverse events

Azithromycin is considered safe for use in pregnancy and is recommended for the treatment of urethritis and cervicitis caused by *Chlamydia trachomatis* and *Neisseria gonorrhoeae*.^19^ Increased risks of malformations have been reported in some observational studies following first trimester exposure to azithromycin or to any macrolide antibiotic,^20–24^ but not in others.^25–28^ In a meta-analysis, azithromycin use (vs alternative antibiotics) in the first trimester was weakly associated with gastrointestinal malformations.^29^ In the second and third trimesters, macrolide exposure was associated with genital malformations, comprised mostly of hypospadias.^20^ One case–control study reported increased relative odds of miscarriage in the first 20 weeks of pregnancy among those prescribed azithromycin.^30^ A limitation of these observational studies is the potential for confounding by indication. In SANTE, participants are enrolled after the first 14 weeks of pregnancy and study personnel are trained to identify and report major congenital malformations as serious adverse events (SAEs). Other events considered as SAEs include pregnancy losses before 22 weeks, maternal deaths, hospitalisations and other significant or life-threatening illnesses. SAEs are reviewed by study physicians and assessed for relatedness to study medication.

In young children, the most common adverse reactions to azithromycin are gastrointestinal symptoms, reported in 1%–4% of those treated.^10 31^ Cardiac toxicity is a potential concern, although the risk is not well established in paediatric populations.^10^ A randomised trial of 450 children aged 6 weeks to 59 months found no severe adverse events in azithromycin-treated children, and only vomiting was reported more frequently in the azithromycin arm.^32^ An association between treatment with erythromycin and infantile hypertrophic pyloric stenosis (IHPS) has been reported in the first 2 weeks of life, and to a lesser extent, in the third through fifth weeks of life.^33^ The relationship between azithromycin and IHPS in infants less than 6 weeks of age is unclear.^34^ In a recent RCT, one case of IHPS was reported among more than 10 000 azithromycin-treated infants fewer than 6 months of age.^35^ The first dose of study medication in SANTE is administered at age 6 weeks or greater, although breastfed infants born to enrolled mothers could be exposed to low levels of azithromycin following the maternal delivery dose.^36^ IHPS is monitored in SANTE as an adverse event of special interest and symptoms are solicited at all infant visits. An algorithm prompts physician review and assessment for relatedness, with any instances of probable or confirmed IHPS reported as SAEs (online supplemental appendix figure 1).

To detect potential harmful associations between azithromycin and the SANTE study endpoints, an independent statistician analyses stillbirths and infant deaths by treatment group at prespecified intervals. The integrity of the trial is maintained by limiting these analyses to the harmful side of the sampling distribution of the hazard and risk ratio statistics. Results are reported to the data safety and monitoring board (DSMB).

### Statistical considerations

#### Sample size and power

The original power calculations for the primary aims were based on anticipated stillbirth and infant mortality rates in the Sikasso/Koutiala regions estimated from published data at the time the trial was being designed (table 3). Analysable endpoints were expected for at least 85% of enrolled participants. After the trial was initiated, observed stillbirth and infant mortality rates in the study population, pooled across blinded treatment arms, were used to update the sample size targets from 33 600 to 49 600 in the mother–infant cohort and from 8500 to 12 000 in the infant-only cohort (online supplemental appendix table 4). The resulting sample sizes are large, as infant mortality even in Mali is relatively rare, resulting in somewhat small absolute differences. For example, for Aim1B, with a baseline IMR of 9/1000, a 24.7% relative reduction means detecting an absolute reduction of less than 3 deaths per 1000.

**Table 3 T3:** Sample size assumptions and minimum detectable relative reductions for the coprimary aims

	Original	Revised
Target sample size, mother–infant cohort	33 600*	49 600

Aim 1A. Effect of intervention on composite outcome of stillbirths and infant deaths from birth to 12 months		
Baseline combined stillbirth and infant mortality rate	105/1000†	74/1000†
Minimum detectable relative mortality reduction, comparing azithromycin to placebo treatment arms		
80% power	9.5%	8.7%
90% power	10.9%	10.1%

Aim 1B. Effect of intervention on infant deaths from first dose (approx. 6 weeks) to 12 months		
Infant mortality rate	28/1000‡	9/1000‡
Minimum detectable relative mortality reduction, comparing azithromycin to placebo treatment arms		
80% power	18.6%	24.7%
90% power	21.4%	28.3%
With addition of infants from the infant-only cohort§		
80% power	16.6%	22.3%
90% power	19.1%	25.6%

*In the original sample size calculation, 15% anticipated loss to follow-up (LTFU) meant that 28 560 infants were expected to have analysable endpoints.

†Original assumed composite baseline stillbirth and infant mortality was 105 deaths per 1000 births, calculated from 33 stillbirths/1000 births^55^ and 74.8 infant deaths per 1000 live births (Sikasso data, Mali 2012 Demographic and Health Survey [DHS] report^56^), assuming that 6–11 months mortality data are available for 90% of infants and subtracting stillbirths from the live birth denominator. Revised observed composite stillbirth and infant mortality rate in the study population is 74 deaths per 1000 births.

‡Original baseline infant mortality rate after 6 weeks of age was 28 per 1000 live births (Sikasso data, 2012 Mali DHS report) assuming that 6–11 months mortality data are available for 90% of infants; revised infant mortality rate after 6 weeks of age was updated to 9 deaths per 1000 live births based on observed mortality in the study population.

§Original target sample size for infant-only cohort was 8500, assuming 7650 analysable (10% LTFU); revised target sample size 12 000.

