## Methods and analysis

### Study design, objectives and hypotheses

Sauver avec l’Azithromycine en Traitant les Femmes Enceintes et les Enfants (SANTE) is an individually randomised, placebo-controlled, double-masked trial. Using a 2×2 factorial design with four treatment arms, SANTE will simultaneously assess coprimary aim 1A: whether azithromycin administered at routine antenatal care (ANC) visits (second and/or third trimester) and at delivery reduces a composite outcome of stillbirth and infant mortality, and coprimary aim 1B: whether azithromycin administered to infants concurrently with the first and third doses of pentavalent vaccine (Penta-1 and Penta-3) reduces mortality from the time of the first dose through 6–12 months of life. We will enrol 49 600 pregnant participants who will be randomised to receive 2 g azithromycin or placebo as a single oral dose twice during pregnancy and at delivery, for up to three total doses. Their infants will be randomised to receive 20 mg/kg azithromycin or placebo as a single oral dose at their routine Penta-1 and Penta-3 vaccination visits (figure 1). According to the national routine immunisation schedule, these vaccination visits occur at approximately 6 and 14 weeks of age, respectively. Infants are followed through at least 6 months and up to 12 months of age. To increase statistical power for aim 1B, a separate cohort of 12 000 infants, the infant-only cohort, is recruited at the Penta-1 visit. Infants enrolled in the infant-only cohort are randomised, dosed and followed in the same manner as those born to pregnant participants. Participant enrolment commenced in September 2020 and is expected to be complete by April 2023.

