#### Interim analysis

There is one prespecified formal interim analysis for efficacy planned for the maternal intervention, to take place when half of the expected number of stillbirths and infant deaths have occurred. This analysis will be run with an interim type I error of 0.007, which is expected to require a maternal intervention relative efficacy of at least 13%. Due to the complexity of this 2×2 factorial design, if this level was reached, the DSMB would consider all available data, and decide whether to stop randomisation to one or both interventions.

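### Table 3 bases its original detectable reductions on analysable participants but its revised ones on full enrolment, so the revised figures allow for no loss to follow-up

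*Protocol article*

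**What the plan says.** All of this is in the protocol article, mainly under Sample size and power.

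- After introducing the original power calculations, the text says "Analysable endpoints were expected for at least 85% of enrolled participants". It then reports that blinded pooled event rates led to revised targets, "from 33 600 to 49 600 in the mother–infant cohort and from 8500 to 12 000 in the infant-only cohort".
- Footnote * of Table 3, attached to the original 33 600, says "15% anticipated loss to follow-up (LTFU) meant that 28 560 infants were expected to have analysable endpoints".
- Footnote § says "Original target sample size for infant-only cohort was 8500, assuming 7650 analysable (10% LTFU); revised target sample size 12 000". It gives an analysable number for the original target and none for the revised one.
- The revised target is an enrolment figure. Study design, objectives and hypotheses says "We will enrol 49 600 pregnant participants who will be randomised to receive 2 g azithromycin or placebo".
- Table 3 gives detectable relative reductions at 80%/90% power. Original: 9.5/10.9% (aim 1A), 18.6/21.4% (aim 1B), 16.6/19.1% (aim 1B with the infant-only cohort). Revised: 8.7/10.1%, 24.7/28.3% and 22.3/25.6%. The text uses the 24.7% figure as a worked example.

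**The concern.** Table 3 is the published account of what the enlarged trial can detect, and it sets two columns side by side as if they were calculated in the same way. If one deducts losses and the other does not, part of the apparent change comes from the change of basis. For aim 1A the printed figures suggest that the enlarged trial became more sensitive, moving from 9.5% to 8.7% at 80% power. With the same deduction in both columns the move is from 9.5% to 9.4%, so the enlargement roughly offsets the lower event rate and does no more. For aim 1B the deterioration from the low observed mortality is understated. The power attached to the revised reductions would also be lower than printed by an amount that depends on retention.

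**Working it through.** **Inputs.** Baseline rates per 1000 from Table 3: 105 (original) and 74 (revised) for aim 1A; 28 and 9 for aim 1B. Enrolment targets: 33 600 and 49 600 mothers; 8500 and 12 000 infants. Allocation is 1:1 at the margin for each intervention. The article does not state the final alpha; two-sided 0.05 is assumed, and it reproduces the printed figures.

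**Formula.** With N/2 per arm, p₁ the baseline rate, p₂ = p₁(1 − r) and p̄ their mean, power = Φ{[(p₁ − p₂) − 1.96·√(2p̄(1 − p̄)/(N/2))] / √([p₁(1 − p₁) + p₂(1 − p₂)]/(N/2))}. This is solved for r at 80% and 90% power.

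**Candidate numbers.**
- Original after loss: 33 600 × 0.85 = 28 560; plus 8500 × 0.90 = 7650 gives 36 210.
- Revised, full enrolment: 49 600; plus 12 000 gives 61 600.
- Revised after the same loss: 49 600 × 0.85 = 42 160; plus 12 000 × 0.90 = 10 800 gives 52 960.

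**Original column** (80%/90% power, %)

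| Aim | Printed | After loss | Full enrolment |
|---|---|---|---|
| 1A | 9.5/10.9 | 9.47/10.92 | 8.75/10.09 |
| 1B | 18.6/21.4 | 18.63/21.39 | 17.24/19.81 |
| 1B + infant-only | 16.6/19.1 | 16.63/19.12 | 15.47/17.79 |

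**Revised column** (80%/90% power, %)

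| Aim | Printed | After loss | Full enrolment |
|---|---|---|---|
| 1A | 8.7/10.1 | 9.44/10.88 | 8.72/10.05 |
| 1B | 24.7/28.3 | 26.67/30.52 | 24.73/28.32 |
| 1B + infant-only | 22.3/25.6 | 23.98/27.47 | 22.34/25.61 |

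The original column matches only after loss, the revised column only at full enrolment. Solving backwards, the printed revised reductions imply N of 49 148–49 818 and 61 646–61 826, which is 99–100% of enrolment. The original ones imply 85–86%. Unpooled variance, a continuity correction, Schoenfeld and Freedman event formulas, reading the baseline as the pooled rate, and one-sided 0.05 were also tried. None reproduces the whole revised column on loss-reduced numbers.

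**Power at the printed reductions.** For aim 1A with r = 8.7%: p₂ = 0.074 × 0.913 = 0.06756 and the difference is 0.006438. With 24 800 per arm the standard error is 0.002303, so z = 0.006438/0.002303 − 1.96 = 0.835 and power is 79.8%. With 21 080 per arm the standard error is 0.002498, so z = 0.617 and power is 73.1%. In the same way:

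| Loss | 1A | 1B | 1B + infant-only |
|---|---|---|---|
| none | 79.8/90.3 | 79.9/90.0 | 79.9/90.0 |
| 5% | 77.8/88.8 | 77.9/88.4 | 77.8/88.5 |
| 10% | 75.6/87.1 | 75.6/86.7 | 75.6/86.7 |
| 15% (infant-only 10%) | 73.1/85.1 | 73.2/84.8 | 73.7/85.2 |

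**The case against.** Several points on the other side have force.

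*The loss rates belong to the original design.* The 85% sentence is in the past tense and next to the original calculations, it says at least 85%, and both footnotes attach their loss rates to the original targets. This stands. It means that 73–74%/85% cannot be presented as the trial's actual power. It does not supply a reason for zero loss in the revised column. The article still defines loss to follow-up and plans to compare it across arms.

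*The observed rates may already absorb loss.* If 74 and 9 per 1000 are deaths over all births, lost participants included, full enrolment gives the right expected number of deaths and a further deduction would count loss twice. This is possible. The article does not say so, and supplemental appendix table 4, to which it refers for the update, is not shown.

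*Lost infants are censored, not dropped.* The primary Cox model keeps an infant until last contact, so for aim 1A an infant lost late has already contributed the early high-risk period. Removing 15% of N therefore probably overstates the information lost. This too supports treating the 15% result as the low end. It does not support a calculation with no loss, and the original column made the same simple deduction. In the other direction, aim 1B counts only infants who reach a first dose, so stillbirths, early deaths and undosed infants also leave its denominator. The article gives no number for these.

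Two stronger readings are tempting and fail. A reader might take the interim threshold of 13% as confirmation that loss was meant to apply, since half the events from 42 160 (1560) give 1 − exp(−2 × 2.697/√1560) = 12.8%, against 11.8% from 49 600. But the original design gives 28 560 × 0.105/2 = 1499 events and 13.0%, so the figure may simply have been carried over. A reader might also infer that a null aim 1B result would be over-interpreted, because the loss-adjusted 27.5% exceeds the 24.9% reduction that the Discussion cites for infants aged 1–5 months. The printed 25.6% already exceeds it, and power for a 24.9% reduction with the infant-only cohort is still about 83% after loss (88% without).

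**Conclusion.** The inconsistency is established: the original column of Table 3 rests on analysable numbers and the revised column on full enrolment. Unless the observed rates already include lost participants in their denominator, the revised reductions are too favourable for any non-zero loss.

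At the originally planned retention, they worsen by about 0.7–0.8 percentage points for aim 1A, about 2.0–2.2 for aim 1B and 1.7–1.9 for aim 1B with the infant-only cohort. Power at the printed values is then about 73–74%/85% in place of 80%/90%. That is a lower bound on the planned retention, not an estimate of what the trial achieved; better retention brings it closer to the printed values. The result assumes two-sided alpha 0.05 and a simple deduction of lost participants. No analysis or decision rule shown in the article depends on these figures. What needs correcting is the stated sensitivity of the trial and the comparison between the columns.

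**What to change.** State the analysable number or retention fraction behind the revised column, in a footnote parallel to those for the original targets. Use the original 85% and 90%, or the observed retention if it is higher, and recompute on that basis. With 85%/90% the revised entries are 9.4/10.9%, 26.7/30.5% and 24.0/27.5%. Update the 24.7% worked example to match. Its message survives, since 26.7% of 9 per 1000 is 2.4 per 1000, still under 3.

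Alternatively, keep the printed figures and say why no deduction is needed, for example because the observed 74 and 9 per 1000 already count lost participants in the denominator. In either case, note that the columns were calculated on different bases if that remains so.

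The cost is a table and footnote correction, with less favourable figures if loss is applied. It needs no additional participants and no change to the analysis.

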### Study setting

SANTE is conducted by investigators at the Centre pour le Développement des Vaccins, Mali (CVD-Mali), an ongoing collaboration between the University of Maryland School of Medicine and the Malian Ministry of Health. For the past decade, much of northern and central Mali has been besieged by political instability and violence. The southwestern region of Sikasso, recently divided into the independent regions of Sikasso and Koutiala, had a reported infant mortality rate of 67 per 1000 live births in 2018.^16^ It was selected as the study setting due to its high under-5 mortality, moderate utilisation of ANC, moderate routine immunisation coverage, and relative security (online supplemental appendix table 2). Malaria is endemic in southwestern Mali, and standard of care for pregnant women is at least three doses of sulfadoxine-pyrimethamine (SP) intermittent preventive treatment (IPTp). Children aged 3–59 months receive a combination of monthly SP plus amodiaquine as seasonal malaria chemoprophylaxis (SMC) for 4 months during peak malaria transmission season (July–October). Each monthly SMC dose is composed of one directly observed dose and two additional doses to be administered at home by the caregiver. In Sikasso, IPTp coverage with three or more doses is 26.8%, and 54% of age-eligible children receive one or more doses of SMC each year.^16^ Within the Koutiala and Sikasso regions, the districts of Koutiala, Kignan and Niena were selected for study operations. These districts represent areas with a high burden of paediatric illness and have populations of sufficient size to meet the study’s enrolment requirement within the target time frame.

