#### Analysis of primary aims

The primary analysis for aim 1A will be according to the intention-to-treat (ITT) principle. All live born infants and all stillborn infants born at ≥22 weeks gestation or weighing at least 500 g will be included, with infants classified according to the treatment assignment made at the time of the mother’s enrolment. For aim 1B, the primary analysis will be according to modified ITT, beginning from the first assigned dose. Sensitivity analyses of the two aims will be modified as-treated. If a mother or infant receives at least one study dose of azithromycin, they will be classified as being in the corresponding azithromycin-receiving study arm. Percent lost to follow-up will be compared across treatment arms for each intervention. Among those lost to follow up, baseline characteristics will be compared to assess whether loss is differential by intervention or by treatment arm. In the 2×2 factorial design, the primary analyses will fit a Cox proportional hazards regression model with two indicator variables for the two interventions, with censoring at the earliest of documented refusal for further participation, death, last study contact or recorded source of vital status, or attainment of 12 months of age. The study is not powered to detect a statistical interaction effect between the two interventions, but if it is important (p<0.05 or ratio of HRs >1. 5 or <0.67), results for all four study arms will also be reported. For primary aim 1A, the analysis timeline will be calculated from delivery, with stillbirths assigned day 0.1. For primary aim 1B, the timeline will start at the receipt of the first infant dose. For a measure of overall public health impact on infant mortality, a supplementary analysis will be done with the timeline starting at the live birth.

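### The revised aim 1B detectable reductions treat every enrolled pregnancy as an analysed infant, although the analysis set is infants who receive a first dose

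*Protocol article*

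**What the plan says.** All references are to the protocol article.

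- **Study design, objectives and hypotheses:** "We will enrol 49 600 pregnant participants who will be randomised to receive 2 g azithromycin or placebo". A separate cohort of 12 000 infants is recruited at the Penta-1 visit to raise power for aim 1B.
- **Randomisation and masking:** infants in the mother–infant cohort are randomised when the mother enrols, before birth.
- **Intervention:** the first infant dose is given at the Penta-1 visit, at 6 weeks of age or later.
- **Table 3:** the aim 1B endpoint is "Effect of intervention on infant deaths from first dose (approx. 6 weeks) to 12 months". The footnote describes the revised rate, which counts deaths beyond the sixth week, as "updated to 9 deaths per 1000 live births based on observed mortality in the study population". The footnote on the infant-only cohort gives "revised target sample size 12 000", with no analysable number beside it.
- **Sample size and power, text:** "with a baseline IMR of 9/1000, a 24.7% relative reduction means detecting an absolute reduction of less than 3 deaths per 1000". At least 85% of enrolled participants were expected to have an analysable endpoint.
- **Analysis of primary aims:** "For aim 1B, the primary analysis will be according to modified ITT, beginning from the first assigned dose". The time axis starts when the infant receives that dose.
- **Study setting:** the area was chosen partly for its "moderate routine immunisation coverage". No coverage figure appears in the text.

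**The concern.** Three different populations meet in one calculation. The multiplier is enrolled pregnancies, the rate is per live birth, and the analysis is of infants who received a first dose. A stillborn infant cannot be in the aim 1B set. Nor can an infant who never attends Penta-1, and that infant's later death drops out too, although a rate per live birth would count it.

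The revised column also appears to have lost the allowance for non-analysable participants that the original column carried.

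Aim 1B is the coprimary aim with few events, so its power depends directly on the number of deaths among dosed infants. If that number is too high in the planning, the trial is described as able to detect a smaller effect than it can. A null result on infant dosing would then be read as stronger evidence than it is.

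**Working it through.** **Method.** Two-proportion normal approximation, 1:1 allocation, two-sided alpha 0.05. The article does not state the final alpha; 0.05 two-sided reproduces Table 3 and one-sided does not. With n per arm, control rate p₁, treated rate p₂ = p₁(1 − r) and mean rate p̄:

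power = Φ{ [(p₁ − p₂) − 1.96·√(2p̄(1 − p̄)/n)] / √([p₁(1 − p₁) + p₂(1 − p₂)]/n) }

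This is solved for r at 80% and 90% power. Deaths below are N × 0.009, that is, at the control rate in both arms.

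**Step 1: reproduce Table 3, aim 1B.**

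| Column | N | Rate | Computed 80%/90% | Printed |
|---|---|---|---|---|
| Original | 28 560 (85% of 33 600) | 28/1000 | 18.6%/21.4% | 18.6%/21.4% |
| Original, combined | 28 560 + 7650 = 36 210 | 28/1000 | 16.6%/19.1% | 16.6%/19.1% |
| Revised | 49 600 | 9/1000 | 24.7%/28.3% | 24.7%/28.3% |
| Revised, combined | 61 600 | 9/1000 | 22.3%/25.6% | 22.3%/25.6% |
| Revised at 85% | 42 160 | 9/1000 | 26.7%/30.5% | no match |

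The original column uses analysable numbers and the revised column uses enrolled numbers. The revised column implies 49 600 × 0.009 = 446 deaths in the mother–infant cohort.

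**Step 2: live births only.** The article gives no revised stillbirth rate, so I use the original planning figure of 33/1000. N = 49 600 × 0.967 = 47 963, with 432 deaths. The detectable reduction is 25.1%/28.8%, and power at 24.7% is 78.6%.

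**Step 3: deaths before 6 weeks.** The composite rate of 74/1000 less 9/1000 leaves about 65/1000 stillborn or dead before 6 weeks, so survivors number 49 600 × 0.935 = 46 376. The rate must then be re-expressed per survivor: 432/46 376 = 9.31/1000. The deaths are the same 432 and the result is again 25.1%/28.8%. No further cut is due.

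**Step 4: add the 85% analysable share.** N = 47 963 × 0.85 = 40 769, with 367 deaths. The detectable reduction is 27.1%/31.0%, and power at 24.7% is about 72%. For the combined cohort, with the original 10% infant-only loss (12 000 × 0.90 = 10 800), N = 51 569. The detectable reduction is 24.3%/27.8%, and power at 22.3% is about 73%.

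**Step 5: add Penta-1 attendance.** The text gives no figure, so 80–95% is an assumption. It is applied to the mother–infant cohort only and is assumed not to overlap the 15% non-analysable share.

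| Assumed attendance | N | Deaths | Reduction at 80% power | Power at 24.7% | Combined: reduction at 80% power | Combined: power at 22.3% |
|---|---|---|---|---|---|---|
| 95% | 38 730 | 349 | 27.7% | 70% | 24.7% | 71% |
| 80% | 32 615 | 294 | 30.0% | 62% | 26.3% | 65% |

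**Step 6: an offset.** The 9/1000 is pooled over masked arms. If the drug truly cut deaths by 24.7%, the placebo rate would be 9/(1 − 0.247/2) = 10.3/1000. Power at 24.7% is then about 84% with 47 963 live births, and about 77% with 40 769.

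**The case against.** The strongest reply is that the part the article documents beyond loss to follow-up is small. Stillbirths cost about 1.4 points of power, less than the imprecision of a rate rounded to 9/1000, and using a pooled rate as the placebo rate more than cancels that. **This stands**, and it is why stillbirths alone would not justify the point. It does not cancel the missing 85% share: with both applied, power at 24.7% is about 77%.

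A reader might infer that N should be cut to 6-week survivors while 9/1000 is kept, giving 25.5%/29.2%. The footnote does not support that. A rate per live birth, multiplied by live births, already gives the right number of deaths after 6 weeks, so the extra cut removes early deaths twice.

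A reader might also infer that the design is shown to deliver only some 300 deaths. The article does not show this, for three reasons:

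- The attendance range is assumed. The remark on coverage describes the region, not women recruited at antenatal care.
- Undosed infants may already be among the 15% counted as non-analysable.
- The observed 9/1000 may already absorb some attrition, because its denominator is not explained.

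Multiple births add a few infants. Under the Cox model, infants lost after dosing still contribute follow-up time. Coverage and the sample-size revision are referred to online appendix tables 2 and 4, which are not shown and may resolve some of this. None of it explains why the two columns of Table 3 rest on different kinds of N.

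**Conclusion.** The point holds in a limited form. Table 3's revised aim 1B figures rest on a population the design cannot deliver, since not every enrolled pregnancy yields a dosed, analysable infant, and the revised column departs from the basis of the original one.

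On the article's own figures (33 stillbirths/1000, 85% analysable, 10% infant-only loss, 9/1000 as the placebo rate), the 80%-power reductions move from 24.7% to about 27.1%, and from 22.3% to about 24.3% in the combined cohort. Power at the printed effects is about 72% and 73% rather than 80%. Most of this comes from the dropped 85% share and little from stillbirths.

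The further loss from infants never dosed is certain in direction if any infant misses Penta-1, but its size is unknown. The assumed range gives 27.7–30.0% (combined 24.7–26.3%). The offsets could recover part of the total. The combined-cohort figures matter most, because that cohort was added for this aim.

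**What to change.** From blinded pooled data, take two quantities: the expected number of infants who receive a first dose and have an analysable endpoint, and the death rate from first dose per 1000 dosed infants. State both denominators, and say whether the 15% non-analysable share includes undosed infants. Print the expected number of aim 1B deaths for the mother–infant and combined cohorts. Then restate the four revised aim 1B figures and the 24.7% worked example, and say whether the rate is used as a pooled or a placebo rate.

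Restoring the 85% share alone (42 160 infants, 26.7%/30.5%) would not be enough, because it still starts from pregnancies rather than dosed infants.

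The cost is a recalculation and a corrected table. No unblinding or change in conduct is needed, but the stated figures will probably be less favourable.
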